#### Exploratory outcomes

##### Sleep quality, architecture, and patterns (main study)

Sleep quality and architecture will be evaluated using polysomnography (PSG; HomeSleepTest REM+, SOMNOmedics AG, Germany). In addition to actigraphy, PSG objectively assesses sleep stages, total sleep time, latency, awakenings, and arousal. PSG testing will be conducted at home between days 1 and 2 at visits A and B. PSG data will be recorded using headband equipment, which the parents will mount at home in the evening on the first day and remove the next morning on the second day. Self-reported data on sleep duration, latency, awakenings, and daytime tiredness/sleepiness will be collected using the Scandinavian Sleep Questionnaire-Children and Adolescents (SSQ-CA) (60).

##### Mental health and overall well-being (main study)

Mental health and well-being will be assessed using several questionnaires. Measures of mood, fatigue, subjective sleepiness, and circadian rhythm, which are domains potentially influenced by sleep extension, will be assessed using the Stanford Sleepiness Scale (61) and the SSQ-CA (60).

Overall well-being and health-related quality of life will be evaluated using the parent-reported Pediatric Quality of Life Inventory (PEDSQL) (62) and the child-reported KIDSCREEN-27 questionnaire (63–65).

Mental health will be assessed using the parent-reported Strengths and Difficulties Questionnaire (66). Stress levels are measured using the Perceived Stress Scale for Children (67) and the Parental Stress Scale for parents (68).

##### Motor skills (main study)

Fine motor control will be assessed using the Purdue pegboard test (Model 32020, Lafayette Instrument Company, USA), and muscular strength will be evaluated using a handgrip strength test (BIMS Digital Grip Dynamometer, Baseline Evaluation Instruments, USA).

##### Blood biomarkers (main and substudy-I)

In the main study, blood samples (∼10 mL) will be collected in the fasting state by venipuncture to measure parameters of glucose homeostasis (e.g., glucose and insulin), lipid profile (e.g., triglyceride, low- and high-density lipoprotein cholesterol), inflammation markers (e.g., C-reactive protein), appetite-regulating hormones (e.g., leptin and ghrelin), sex hormones (e.g., estrogen and testosterone), and isolated peripheral blood mononuclear cells. For children participating in substudy-I, an additional 2-hour blood sample (∼10 mL) will be collected after the meal test.

##### Brain structure, activity, and connectivity (substudy-II)

Participants will undergo whole-brain structural, functional, and diffusion MRI on a 3 Tesla Siemens Magnetom Vida scanner (Siemens, Erlangen, Germany) using a 64-channel head coil at the DRCMR. Prior to scanning, children will be familiarized with the MRI environment using an MRI simulator. High-resolution T1-weighted and T2-weighted images will be acquired using 3D magnetization prepared 2 rapid acquisition gradient echo (MP2RAGE) (69) and 3D T2 SPACE sequences. These structural images will be used to quantify apparent cortical thickness, cortical volume, surface area, subcortical volumes, and structural covariance. In addition, the MP2RAGE provides an R1 map, which is sensitive to myelin content, and may therefore be relevant for assessing plastic changes related to the sleep extension intervention. Multi-shell diffusion MRI will be used to map the microstructural characteristics of the white matter and subcortical grey matter regions and to assess anatomical connectivity. Functional MRI will be collected during passive movie watching, allowing investigation of functional connectivity in a naturalistic setting (70).

#### Other measures

##### Socioeconomic status (main study)

Information on income, parental education, employment status, ethnicity, and immigration background will be obtained through a demographic questionnaire completed by parents during screening. These parameters will be used to classify children and their families into high or low socioeconomic strata (binary) to examine their potential influence on study outcomes and to tailor the intervention within each family's framework.

##### Puberty stage (main study)

A short questionnaire completed by the parents will assess the child's puberty stage (I-5) according to the Tanner stage classification method (71, 72), based on genital development and pubic hair status in boys, and breast development and pubic hair status in girls.

### Sample size determination

Sample size calculations were designed to achieve 80% statistical power (corresponding to a type II error of 0.2). Two-sided hypothesis testing with a type I error rate of 2.5% (i.e., *P* ≤ 0.025) was chosen because there are two co-primary outcomes, and a 20% dropout rate over 12 weeks was assumed.

A previous study on sleep extension in children aimed for moderate-to-large effect sizes, Cohen's *d* = 0.58, based on preliminary data (21). This study aims to achieve a similar effect size, resulting in an absolute difference in the final BMI z-score of 0.52 units between groups. We consider this effect size to be appropriate and clinically relevant, as studies of lifestyle interventions in children have demonstrated important clinical benefits with decreases in BMI z-score of 0.25–0.50 units (73).

In a previous study of sleep extension in children, including children of any weight status, a mean BMI z-score of 0.9 was reported, with a standard deviation of 0.9 (21). Based on these data, we assume a mean baseline BMI z-score of +1.0. Under these assumptions, we estimate we will need 114 children assigned in a 1:1 ratio between the active and control groups to detect an effect size of d = 0.58. Although sleep intervention studies in children report dropout rates below 4% (21), we based our calculations on a more conservative 20% attrition rate (i.e., five times higher than previously observed but more realistic for our longer study duration and more demanding assessment). We estimated that we would need to enroll 142 children (for 114 completers).

Considering learning and memory, we defined our co-primary outcome as overall 24 h learning. Previous studies on sleep extension in children have found moderate effect sizes for improved performance in the cognitive domain, corresponding to similar effect sizes for the academic performance domain (31). We have not found studies investigating the effects of sleep or sleep extension on 24 h learning effects. In recent experiments, we found that overnight sleep is related to total 24 h skill learning in children and that children benefit from offline learning effects compared to adolescents and young adults (41). Based on the mean performance and standard deviation at baseline among school-aged children aged 8–10 years, we anticipate that a sample size of 142 will allow us to detect a moderate-to-large effect size in the learning and memory domain at *P* ≤ 0.025, with 80% power.

The two substudies are exploratory studies designed to provide mechanistic insights. Therefore, we did not conduct power calculations separately for the two substudies. Instead, we selected the respective sample sizes based on previous studies using DLW to measure changes in TEE, which typically include groups of 20–60 children (74–76), and longitudinal studies of MRI-determined changes in brain structure and connectivity, which typically recruit 47–78 children per group (77–80) and rarely more (33).

### Randomization and blinding

After completion of baseline assessments (Visit A), the children will be informed of their group allocation by receiving a sealed envelope. The children will be randomized in a 1:1 ratio to the sleep extension or control group. To ensure balance between the two groups, randomization is stratified by sex (male or female), age (≤9 or >9 years), and participation level (main study only; main+substudy-I; main + substudy-II; main + substudy-I and -II), with each combination defining a stratum. The allocation is determined by a computer-based algorithm implemented in an Excel file. The algorithm is configured such that the probability of allocation depends on the current distribution of participants across groups, thereby maintaining balance between the sleep and control groups and within each stratum. This file is stored as a restricted-access file available only to designated staff for the randomization task. The allocation is subsequently recorded in an electronic case report form within the Research Electronic Data Capture (REDCap) system.

The behavioral nature of the intervention precludes blinding of children and their parents. Nonetheless, staff assessing outcomes and analyzing the data will be blinded to group allocation.

### Data management

Data will be recorded in electronic case report forms (CRF) in a secure REDCap database or on paper CRF. Data recorded on paper CRFs will be converted to electronic records within 5 days. Access to the REDCap database is restricted to authorized staff. Participants are assigned a unique study identification number to ensure de-identification of research data. To ensure data control, REDCap's built-in setup is used, which automatically notifies study staff about missing data. Source data from DXA scans, ventilated hoods, MRI, PSG, and analysis of biological material are registered in the relevant device interface software. All personal data and biological material are handled confidentially and stored in accordance with applicable law, GDPR, and the Danish Data Protection Act. (No. 502 of 23rd May 2018). For data collected from external sources (e.g., MyFood24 and CambridgeCognition), data are handled in accordance with data processing agreements. Study-related monitoring and audits by the principal investigator, the Institutional Review Board/Independent Ethics Committee, or regulatory inspections will be permitted. Direct access to the source data, CRFs, and other relevant materials will be provided. Source data will be cleaned and analyzed independently for each parameter by staff members blinded to group allocation. After the extraction of predefined parameters, the datasets will be merged into an analysis dataset using a secure data management platform.

### Statistical analysis

#### Baseline characteristics

Results for baseline characteristics will be reported as mean (standard deviation) for normally distributed variables and as median (interquartile range) for non-normally distributed variables. Categorical variables will be reported as frequency counts and percentages.

#### Primary analysis

The effect of the intervention will be evaluated using linear mixed-effects models (LMMs) estimated with restricted maximum likelihood (REML), allowing inclusion of all available observations in the statistical model without imputations.

The LMMs will be performed with fixed effects for group, time, and the group-by-time interaction, with participant included as a random effect. The primary model will include baseline and 12-week measurements. An extended model with 3 time points (baseline, 12 weeks, and 6 months) will be developed to assess the sustainability of effects over the follow-up period. These models will be adjusted for stratification variables and baseline pubertal stage, included as fixed main effects. Model assumptions will be evaluated using residual diagnostics. If model assumptions are not met, appropriate transformations will be considered.

The primary analysis will be conducted using an intention-to-treat approach, including all randomized children according to their group allocation, regardless of whether or not they complete the study.

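### The primary mixed model leaves baseline means free by group and enters covariates as main effects only, so the stated adjustment adds almost no precision and baseline information is discarded

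*Protocol article*

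**What the plan says.** All of this is in the protocol article. The Primary analysis section fixes the terms of the model: "The LMMs will be performed with fixed effects for group, time, and the group-by-time interaction, with participant included as a random effect". On the rows used it says "The primary model will include baseline and 12-week measurements", so baseline is an outcome row and not a covariate. On adjustment it says "These models will be adjusted for stratification variables and baseline pubertal stage, included as fixed main effects". Estimation is by REML, "allowing inclusion of all available observations in the statistical model without imputations". A second model covers follow-up: "An extended model with 3 time points (baseline, 12 weeks, and 6 months) will be developed to assess the sustainability of effects".

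The Abstract defines both co-primary outcomes as change from baseline to 12 weeks, so the treatment effect is the group-by-time term, although the section does not name the contrast. Under Randomization and blinding, allocation follows the baseline visit and is stratified by sex, age group and four participation levels.

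The Sample size determination section is built on a comparison of final values, "resulting in an absolute difference in the final BMI z-score of 0.52 units between groups", with d = 0.58, SD 0.9, two-sided alpha 0.025, 80% power and 20% dropout. It states no correlation between visits.

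**The concern.** Baseline is measured before randomisation, so the true group difference there is zero. A free group main effect estimates that difference anyway, and its sampling error passes into the group-by-time term.

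A covariate that does not vary with time, entered as a main effect, shifts a child's two visits equally. It therefore drops out of the within-child difference that identifies the treatment effect. A report could then describe the effect as adjusted for sex, age, participation level and puberty when it is in substance unadjusted.

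The stake is precision, mainly for 24 h learning. That outcome is already a difference between two test days within each visit, so its correlation across 12 weeks may be modest.

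**Working it through.** **1. The plan's own figure.** For a final-value comparison, n per arm = 2(z₀.₉₈₇₅ + z₀.₈)²/d² = 2(2.241 + 0.842)²/0.58² = 56.5, so 57 per arm and 114 in total, as stated. Then 114/0.8 = 142.5 against 142 stated, an immaterial difference. With the noncentral t, 57 per arm gives 79.4% power.

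**2. Variance of each contrast.** Take equal SD at both visits and correlation r:
- SD of change = SD × √(2(1−r))
- SD after baseline adjustment = SD × √(1−r²)
- variance ratio, adjusted to change = (1−r²)/(2(1−r)) = (1+r)/2

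The ratio is below 1 for every r < 1. The change contrast is noisier than the final-value comparison used for sizing when 2(1−r) > 1, that is, when r < 0.5.

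**3. Power.** Inputs: 57 per arm, d = 0.58 in single-visit SD units, two-sided alpha 0.025, noncentral t. Both r and the use of 0.58 for learning are assumptions. Example at r = 0.3: the standardised effect is 0.58/√1.4 = 0.490 for change and 0.58/√0.91 = 0.608 after adjustment.

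| r (assumed) | Variance ratio | Power, change | Power, baseline-adjusted |
|---|---|---|---|
| 0.2 | 0.60 | 57% | 81% |
| 0.3 | 0.65 | 64% | 83% |
| 0.5 | 0.75 | 79% | 90% |
| 0.7 | 0.85 | 96% | 98% |
| 0.9 | 0.95 | about 100% | about 100% |

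**4. Do the covariates act?** REML random-intercept models were fitted to simulated data with 71 per arm and with sex given an effect on change.

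*Complete pairs.* The adjusted model, the unadjusted model and the two-sample comparison of change agree exactly. In one dataset at r = 0.5, all three gave −0.6055 with SE 0.1574.

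*20% of week-12 values missing at random.* Mean SE over 40 datasets per row:

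| r | Planned model | Same, no covariates | Completer change score | Common baseline mean |
|---|---|---|---|---|
| 0.3 | 0.2148 | 0.2155 | 0.2231 | 0.1815 |
| 0.5 | 0.1840 | 0.1844 | 0.1892 | 0.1643 |
| 0.9 | 0.0876 | 0.0877 | 0.0882 | 0.0857 |

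The covariates lower the SE by 0.3%, 0.2% and 0.1% (for example 1 − 0.2148/0.2155 = 0.3%). The common-baseline model, with the same main-effect covariates, has a variance ratio to the planned model of (0.1815/0.2148)² = 0.71, (0.1643/0.1840)² = 0.80 and (0.0857/0.0876)² = 0.96.

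**5. Three-visit model.** Visits at weeks 0, 12 and 38 give lags of 12, 26 and 38 − 0 = 38 weeks. A participant random intercept alone imposes the same correlation at all three lags. If correlation falls with time, the 38-week SE is misstated. The document gives no covariance from which to size this.

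**The case against.** The strongest defence is that the analysis is conventional and valid. Randomisation makes the group-by-time contrast unbiased, it targets the stated outcome (change to 12 weeks), and it keeps every randomised child with data. All of that stands.

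Four stronger readings are tempting, and the document does not support them:

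- *A reader might infer that the adjustment does nothing and that the model is simply a change-score test.* This is exact only for complete pairs. With 20% missing and all available data used, the planned model's estimates differed from the completer change score by up to 0.15 at r = 0.3, and the covariates moved single estimates by up to 0.06. It is the precision gain that is negligible.
- *A reader might infer that the trial will miss its 80% power.* That needs r below about 0.5, and no r is given. For BMI z-score, the only outcome with a stated effect size and SD, a high r would put power well above 80% under either analysis. For learning, the sample size section speaks only of a moderate-to-large effect, so 0.58 is borrowed. The 57 per arm also assumes the full 20% dropout, which the section itself calls conservative.
- *A reader might infer an inflated error rate at follow-up.* If change variance were exactly proportional to lag, the random-intercept model would average 12, 26 and 38 to 25.33 and report √(25.33/38) = 0.816 of the proper 38-week SE. Nothing in the document supports that covariance. The three-visit model is also not the primary one, and Table 1 schedules no learning test at Visit C.
- *A reader might infer that puberty is known to drive 12-week change in BMI z-score.* The document does not say so. The point rests on how the covariates enter the model.

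**Conclusion.** The point holds as an efficiency flaw and a largely ineffective adjustment; it does not make the primary analysis invalid. The specified two-visit model yields the raw difference in mean change when all pairs are complete, and something close to it under planned attrition. Relative to baseline adjustment, the complete-pair variance is larger by a factor of 2/(1+r): about 1.05 at r = 0.9, 1.33 at r = 0.5 and 1.54 at r = 0.3. For BMI z-score this is trivial if r is high. For 24 h learning it could cost roughly 10 to 25 percentage points of power over r = 0.5 down to 0.2, given the assumed d of 0.58 and 57 per arm. The three-visit covariance is a secondary point of unknown size. Severity: should fix.

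**What to change.** In the primary model, drop the group main effect at baseline: fit time and group-by-post-baseline-time with a common baseline mean, and keep all available observations under REML. Enter the stratification factors and pubertal stage with covariate-by-time terms, so that the adjustment reaches the treatment contrast. Collapse sparse pubertal stages if needed.

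ANCOVA of the 12-week value on group, baseline value and the same covariates is a close alternative for children with a week-12 value. It is not identical under dropout, because it omits children without that value.

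In the three-visit sustainability model, prefer an unstructured within-child covariance to a random intercept alone.

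The cost is a change of analysis wording, made before unblinding, with no new data. With all factors categorical, the covariate-by-time terms add up to nine parameters (sex 1, age group 1, participation level 3, five pubertal stages 4), fewer if stages are collapsed.

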### Study design

More2Sleep is a two-arm, parallel, randomized controlled trial in 142 children who are allocated in a 1:1 ratio to either an intervention group (*n* = 71, sleep extension) or a control group (*n* = 71, habitual sleep schedule). The study has one main level of participation (all 142 children) and two additional voluntary levels: substudy-I (*n* = 60; 30 children per group) and substudy-II (up to *n* = 142; 71 children per group).

The study consists of a 12-week active intervention and a 6-month inactive follow-up (i.e., 38 weeks post-randomization). During this inactive follow-up period, no contact with the research team will take place. However, families in the sleep extension group will be instructed to continue putting their child to bed 60–90 min earlier. The overall study design is illustrated in Figure 1. All children will be assessed at three time points: baseline (Visit A), at the end of the active intervention (Visit B, week 12), and at the end of the 6-month follow-up (Visit C). During the intervention period, participants in both groups will attend 6 sessions with a family advisor, combining in-person and virtual formats over 12 weeks, to ensure consistent and equal contact frequency with the research team.

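### If within-child correlation falls with time, the three-visit sustainability model, as stated, gives the baseline-to-week-38 group contrast too small a standard error

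*Protocol article*

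**What the plan says.** The Primary analysis section of the protocol article specifies linear mixed models "estimated with restricted maximum likelihood (REML), allowing inclusion of all available observations", with "fixed effects for group, time, and the group-by-time interaction", and "with participant included as a random effect". No other random effect and no residual covariance is named.

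Two versions are described. For the first, "The primary model will include baseline and 12-week measurements". For the second: "An extended model with 3 time points (baseline, 12 weeks, and 6 months) will be developed to assess the sustainability of effects over the follow-up". Residual diagnostics are planned, and one remedy is given: "If model assumptions are not met, appropriate transformations will be considered".

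The Study design section fixes the schedule: "The study consists of a 12-week active intervention and a 6-month inactive follow-up (i.e., 38 weeks post-randomization"). Visits A, B and C therefore fall at weeks 0, 12 and 38. Table 1 shows BMI z-score and DXA body composition at all three visits. The motor learning and word memory tests appear at Visits A and B only.

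**The concern.** A random intercept with independent residuals implies a single correlation for every pair of visits. The model then treats a 38-week change as no more variable than a 12-week change. With gaps of 12, 26 and 38 weeks, and outcomes that drift within a growing child, the longer change would be expected to vary more.

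The model pools the three change variances into one. If correlation decays, the pooled value is too small for the longest interval and too large for the shortest. A statement that an effect on BMI z-score or body fat is still present at 6 months, when based on the change from baseline to week 38, would then carry a confidence interval that is too narrow and a false-positive rate above the stated level. A transformation changes the scale of the outcome. It does not free the model from having one common correlation.

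**Working it through.** **Inputs from the article**
- Visits at weeks 0, 12 and 38, giving gaps of 12 (A–B), 38 − 12 = 26 (B–C) and 38 (A–C) weeks.
- Two-sided thresholds of 0.025 for primary outcomes and 0.05 for secondary and exploratory outcomes. The article does not say which applies to the 6-month BMI z-score, so both are shown.
- 114 completers, 57 per arm. This reproduces: 2 × (2.241 + 0.842)² / 0.58² = 56.5, rounded up to 57 per arm. Dividing by 0.8 for dropout gives 142.5, against 142 stated.

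The article states no error rate for the follow-up test, so there is no figure of that kind to reproduce.

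**Assumed inputs**
- Between-visit correlations, which the article does not give. A range is used.
- Equal variance at each visit, complete data, no true group effect.

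**Formula**

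With complete data the random-intercept REML test uses one within-child variance, proportional to the mean of (1 − r) over the three visit pairs. The true variance of a change between visits i and j is proportional to 1 − r_ij. Hence

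- variance ratio (true / model) = (1 − r_ij) / mean(1 − r)
- actual type I error = 2 × [1 − Φ(z / √ratio)], with z = 1.960 at 5% and 2.241 at 2.5%.

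**Worked example**

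Take r = 0.97, 0.935, 0.905 for gaps of 12, 26 and 38 weeks, so that 1 − r is proportional to the gap. The mean of 1 − r is (0.030 + 0.065 + 0.095)/3 = 0.0633. For weeks 0–38 the ratio is 0.095/0.0633 = 1.50, so the model's standard error is 1/√1.50 = 0.82 of the true one. Type I error is 2 × [1 − Φ(1.960/1.225)] = 11.0% at nominal 5%, and 2 × [1 − Φ(2.241/1.225)] = 6.7% at nominal 2.5%.

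**Range** (actual type I error, in %, at nominal 5% / 2.5%)

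| Assumed r (A–B, B–C, A–C) | Ratio, 0–38 | Weeks 0–38 | Weeks 12–38 |
|---|---|---|---|
| 0.97, 0.935, 0.905 | 1.50 | 11.0 / 6.7 | 5.3 / 2.7 |
| 0.90, 0.796, 0.716 (exponential decay) | 1.45 | 10.3 / 6.3 | 5.5 / 2.8 |
| 0.95, 0.93, 0.90 | 1.36 | 9.3 / 5.5 | 4.5 / 2.2 |
| 0.95, 0.92, 0.90 | 1.30 | 8.6 / 5.0 | 5.5 / 2.8 |
| 0.95, 0.95, 0.93 | 1.24 | 7.8 / 4.4 | 3.7 / 1.7 |
| 0.50, 0.223, 0.111 (exponential decay) | 1.23 | 7.7 / 4.3 | 5.9 / 3.1 |
| 0.95, 0.93, 0.92 | 1.20 | 7.4 / 4.1 | 5.6 / 2.9 |
| 0.90, 0.90, 0.90 (equal) | 1.00 | 5.0 / 2.5 | 5.0 / 2.5 |
| 0.90, 0.95, 0.95 (A–C above average) | 0.75 | 2.4 / 1.0 | 2.4 / 1.0 |

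**Simulation check**

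40,000 null trials per scenario, 57 per arm, analysed by split-plot ANOVA, which equals the random-intercept REML fit when data are complete. Weeks 0–38 rejected 10.5% / 6.3% for exponential decay from 0.90, 9.2% / 5.3% for 0.95, 0.93, 0.90, and 4.9% / 2.5% for equal correlations of 0.90. The two-degree-of-freedom group-by-time test was only mildly affected under decay, at 2.6–3.6% for nominal 2.5%. A test that used only the contrast's own variance, which is what an unstructured covariance amounts to here, stayed at 4.8–5.2% and 2.3–2.6%.

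**The case against.** The strongest reply is that the article does not call participant the only random effect, names no residual covariance, and says that the extended model is still to be developed. An analysis plan that is not shown could add a residual structure. This stands as a caution: the point is a weakness of the model as stated, not a proven error. It does not remove the point, because the article does name the random-effects structure and does name a remedy, and that remedy cannot repair the correlation pattern.

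The second reply is that sustainability over the follow-up period may equally mean the change from week 12 to week 38, and the article names no contrast. This also stands. Under decaying correlation that contrast runs at 1.7–3.1% for nominal 2.5%. The inflation belongs to the change from baseline.

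Several stronger readings are tempting and are not supported:
- A reader might infer that the 6-month test rejects too often whatever the data. It does not: with equal correlations it is nominal, and with an A–C correlation above the average it is conservative. The 11% figure needs 1 − r proportional to the interval, with no constant noise component.
- A reader might infer that the model biases the effect towards appearing sustained. With complete data the group-by-time estimates do not depend on the covariance structure; only the standard errors do.
- A reader might infer lost power at 12 weeks. Within the three-visit model, and with 1 − r proportional to the gap, a correct 80% test at 2.5% would fall to P(Z > 2.241 × 1.453 − 3.083) = 43%, where 1.453 = √(25.33/12) and 25.33 is the mean gap. But the article assigns the 12-week effect to the two-visit model, which has only one correlation and cannot be affected.

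**Conclusion.** The concern holds in conditional form. On its ordinary reading, the extended model imposes one common correlation on visits 12, 26 and 38 weeks apart. If correlation falls with the interval, the baseline-to-week-38 group contrast has a type I error of about 7–11% at nominal 5% and 4–7% at nominal 2.5%, with correspondingly narrow intervals.

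This rests on three things that the article does not settle: the between-visit correlations, the absence of any further residual structure, and the use of the change from baseline as the 6-month contrast. The calculation also takes 57 per arm at week 38, although the 20% dropout allowance covers only the first 12 weeks. The variance ratio does not depend on the sample size, so further loss spread evenly would change the result little.

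The scope is the follow-up analysis of outcomes measured at all three visits. Neither co-primary analysis at 12 weeks is touched.

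**What to change.** In the extended model, replace the participant random intercept with an unstructured 3×3 residual covariance by visit, fitted by REML with Kenward-Roger or Satterthwaite degrees of freedom. Name the 6-month group contrast, and base the sustainability statement on that contrast and its confidence interval. Apply this to every outcome measured at Visits A, B and C. The two-visit primary model can stay as it is.

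The change takes a sentence or two of analysis text before unblinding. SPSS and R, the two programs that the article names, can both fit the model. It uses six covariance parameters instead of two, which 114 to 142 children can support. If correlation decays, the 6-month interval will be wider, as it should be; if the correlations turn out equal, almost nothing is lost.
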